#### 9.4 Follow-up of Adverse Events

The investigator should follow all AEs until occurrence of any of the following situations,

- AE is relieved or improved to baseline level;
- Investigator confirms no further improvement is expected;
- Subject died;
- Subject lost to follow-up;
- The investigator confirmed that the AE was not related to the study treatment;
- Subject starts a new anticancer therapy;
- No clinical or safety data will be collected, or the database will be finally closed.

The final outcome of each AE, including date of AE resolution or death, must be recorded on the CRF/eCRF.

#### 9.5 Criteria for judging the correlation between drugs and adverse events

The investigator should assess the possible association between adverse events and the study drug. See the following 5 criteria for judgment.

- (1) Whether there is a reasonable temporal sequence between medication and the occurrence of adverse reactions;
- (2) Whether the reaction conforms to the known type of adverse reaction of the drug;
- (3) The reaction is relieved or disappeared after drug withdrawal or dose reduction;
- (4) Whether the same reaction occurs again after re-administration of the suspected drug;
- (5) Whether the reaction can be explained by the effect of concomitant drugs, progression of the patient's condition or other treatment measures;

Table 7 Form for Judging the Relationship between Adverse Event and Drug

|                    | 1 | 2 | 3 | 4 | 5 |
|--------------------|---|---|---|---|---|
| Definitely related | + | + | + | + | - |
| Probably related   | + | + | + | ? | - |

|                      |   |   |    |   |    |
|----------------------|---|---|----|---|----|
| Possibly related     | + | - | ±? | ? | ±? |
| Unlikely related     | - | - | ±? | ? | ±? |
| Definitely unrelated | - | - | -  | - | -  |

Note: + indicates yes, — indicates no, ± indicates difficult to confirm or deny, ? indicates that the situation is unknown

The three items judged as definitely related, probably related, and possibly related to the results were counted as adverse reactions, and the incidence of adverse reactions was calculated accordingly.

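### Causality Table 7 has no row for an adverse event with a clear alternative cause, and its Definitely unrelated row requires that there be none

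*Protocol*

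**What the plan says.** Section 9.5 asks the investigator to judge each adverse event on five criteria: timing, known reaction type, response to withdrawal or dose reduction, response to re-administration, and an alternative cause. The last is worded "Whether the reaction can be explained by the effect of concomitant drugs, progression of the patient's condition or other treatment measures".

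Table 7 then gives five rows of answers, from "Definitely related" to "Definitely unrelated". Its legend reads + as yes and − as no; the sign ± "indicates difficult to confirm or deny, ? indicates that the situation is unknown".

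Below the table, the analysis rule follows: "The three items judged as definitely related, probably related, and possibly related to the results were counted as adverse reactions", and the adverse-reaction incidence is computed from them. Section 11.3.5 tabulates drug-related TEAEs, drug-related TEAEs of grade 3 and above, drug-related SAEs, and drug-related TEAEs leading to interruption or termination. No other rule for assigning relatedness appears in the protocol.

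**The concern.** Criterion 5 is the only one of the five on which a yes speaks against the drug. An event that plainly has another cause should move towards unrelated. In Table 7 it cannot: a yes on criterion 5 appears in no row, and the strongest unrelated category asks for a no.

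Both unrelated rows also ask for a no on timing. An event that arises on treatment in a plausible time sequence, but is clearly due to a concomitant drug, therefore fits neither of them.

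At stake is the split between related and unrelated events, which feeds the secondary safety results. It also matters outside the tables: section 9.4 lets follow-up of an event end once it is confirmed as not related, and section 9.6.2 uses correlation with the drug in the assessment of serious events. With no control arm, this split is the main means of attributing events to the drug.

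**Working it through.** The protocol gives no figure on this point to reproduce. The check is a reading of Table 7 followed by a count.

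**Inputs** (section 9.5, Table 7):

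| Row | 1 timing | 2 known type | 3 withdrawal | 4 re-administration | 5 other cause |
|---|---|---|---|---|---|
| "Definitely related" | + | + | + | + | − |
| "Probably related" | + | + | + | ? | − |
| "Possibly related" | + | − | ±? | ? | ±? |
| "Unlikely related" | − | − | ±? | ? | ±? |
| "Definitely unrelated" | − | − | − | − | − |

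**Step 1, column 5.** It reads −, −, ±?, ±?, −. The entry + never occurs. The last row carries the same entry as the first two.

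**Step 2, column 1.** The two unrelated rows both carry −. Timing of + leaves only the three rows that count as adverse reactions.

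**Step 3, coverage by the table's own legend.** With four possible answers on five criteria there are 4^5 = 1024 patterns, of which 4^4 = 256 have + on criterion 5. The rows accept 1 + 1 + (2 × 2) + (2 × 2) + 1 = 11 of the 1024, and 0 of the 256. With yes/no answers only, they accept 2 of 32, and 0 of the 16 with + on criterion 5. The pattern (−,−,−,−,+), an event clearly due to something else, has no row. The pattern (−,−,−,−,−), with no other explanation, is Definitely unrelated.

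**Step 4, more lenient readings.**
- If ± meant either + or −, 8 of the 256 would fit: 4 in Possibly related and 4 in Unlikely related.
- If every ± or ? cell accepted any answer, 32 would fit, 16 in each of those two rows.
- The legend supports neither reading, and under all three Definitely unrelated accepts 0.

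**Step 5, which row is closest.** I counted the cells that differ under the literal reading, for two timely events with a clear other cause:

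| Pattern | Definitely related | Probably related | Possibly related | Unlikely related | Definitely unrelated |
|---|---|---|---|---|---|
| (+,−,?,?,+) | 4 | 3 | **1** | 2 | 4 |
| (+,−,−,−,+) | 4 | 4 | 3 | 4 | **2** |

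The first pattern is closest to a counted row, the second to an uncounted one. The direction depends on the pattern.

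**Step 6, changing one cell only.** With criterion 5 of Definitely unrelated set to +, 1 of the 256 patterns fits. Both patterns in Step 5 still have no row, because column 1 still excludes them from the unrelated rows.

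**The case against.** Four arguments weigh against the point, and each has some force.

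**Progression events are mostly handled elsewhere.** Section 9.3 says that events clearly in line with expected tumour progression are not adverse events, so they never reach Table 7. A reader might infer that the table moves sarcoma events into the related column; the documents do not support that for clear progression. What remains is concomitant drugs, other treatment, and progression that is not clear-cut. Deaths are unsettled: section 9.3 says a death from tumour progression is not recorded as an AE or SAE, while section 9.6.1 says it is reported as an SAE during the trial or safety reporting period. Those two passages must be reconciled.

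**The table is a guide to judgement, not an algorithm.** Only 11 of 1024 patterns match a row literally, so investigators must interpolate in any case. This stands, and it probably softens the effect in practice. It does not excuse a guide that points the wrong way on the one criterion that argues against the drug.

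**The inverted cell lies outside the count.** Definitely unrelated is not among the three counted categories, so that cell alone adds no event to the adverse-reaction incidence. The two strongest related rows are coherent on criterion 5. Summaries of all AEs, TEAEs and SAEs do not use the table, and section 11.3.2 plans no hypothesis test. All of this is correct.

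**A misprinted or misread sign in one cell cannot be ruled out.** Step 6 shows that the gap remains even if that cell should read +.

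**Conclusion.** Table 7 is wrong as written, with minor severity. No row accepts a yes on alternative cause, Definitely unrelated requires a no, and a timely event with a clear other cause has no valid row. The first and third statements rest on the table's own legend; the second holds under every reading tried.

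A reader might go further and conclude that the adverse-reaction incidence will be inflated. The protocol does not show that. It has no nearest-row rule, the closest row changes with the pattern, and nothing says how many such events will occur or how sites will place them. Neither size nor direction of the effect on adverse reactions, related TEAEs or related SAEs can be computed. One misclassified subject weighs 1/10 = 10 percentage points in a cohort of 10, 1/30 = 3.3 in one of 30 and 1/100 = 1 in 100 subjects overall, but that is true of any misclassification and is no estimate of this one.

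**What to change.** Change the two unrelated rows together and add a sentence:

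- Set criterion 5 to + for Definitely unrelated.
- Let criterion 5 be + or ± for Unlikely related.
- Let criterion 1 be + or − in both rows when criterion 5 is +. Without this, the sentence below would contradict column 1.
- State that an event with plausible timing but a clear alternative cause is classed as unlikely related or unrelated.

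With these entries, (+,−,−,−,+) fits Definitely unrelated and (+,−,?,?,+) fits Unlikely related. Read literally, 2 + (2 × 2) = 6 of the 256 patterns with + on criterion 5 then have a row, so the sentence carries most of the weight and should not be left out. The pattern (−,−,−,−,−) loses its present row; the sponsor should say where it belongs.

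The cost is a few table entries and one sentence, with the same wording in the eCRF completion guidelines. Because causality is assigned at the site, the correction should precede data entry. Events already classified with a clear alternative cause would need a second look.

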## 9.6 Serious Adverse Events

### 9.6.1 Definition of Serious Adverse Events

An adverse event is classified as serious when the subject experiences an adverse event that meets one or more of the following criteria after receiving the investigational product: death, is life-threatening, results in persistent or significant disability or incapacity, requires or prolongs patient hospitalisation, is a congenital anomaly or birth defect, follows a pregnancy (spontaneous or induced abortion, termination of pregnancy for medical reasons), and is an important medical event (not immediately life-threatening or results in death, but may jeopardise the subject or may require intervention to prevent one of the other outcomes listed above).

Disease progression, including signs and symptoms of progression, should not be reported as a serious adverse event, but death due to disease progression should be reported as a serious adverse event if it occurs during the trial or safety reporting period. During the trial or safety reporting period, if the final outcome of cancer is death, the event that led to death must be reported as a serious adverse event.

### 9.6.2 Handling of Serious Adverse Events

For any serious adverse event occurred during the clinical trial, the investigator should report to the designated mailbox of PV Department of the sponsor in written form within 24 hours after being informed ([contact]), followed by detailed

and written follow-up reports in a timely manner. For the reporting of death events, the investigator should provide the sponsor and the Ethics Committee with other required data, such as autopsy report and final medical report. Upon receipt of a serious adverse event, the sponsor shall analyze and evaluate it immediately, including seriousness, correlation with the investigational drug and whether it is an expected event. For suspected and unexpected serious adverse reactions, the sponsor should report them to all investigators participating in the clinical trial of investigational drug, clinical trial institutions and ethics committee in an expedited manner; and the investigator should report suspected and unexpected serious adverse reactions provided by the sponsor to the ethics committee. Suspected and unexpected serious adverse reactions should also be reported by the sponsor to drug regulatory authorities and health authorities.

### **9.7 Common Adverse Events Disposal measures**

Refer to Treatment Recommendations for Immune-related Adverse Events Caused by Immune Checkpoint Inhibitor Therapy and Chinese Society of Clinical Oncology (CSCO) Guidelines for the Management of Immune-Checkpoint Inhibitor-associated Toxicity 2019 for the treatment recommendations for adverse events caused by TQB2858 injection.

## **10. Data Management**

See Data Management Plan and standard operating procedures of data management department for details.

### **10.1 Data Entry**

An electronic data capture system (EDC) was used for data collection and management in this trial. The investigator or clinical coordinator should timely, accurately, completely and normatively enter the source data information into EDC according to the 《eCRF Completion Guidelines》. Only the investigator or clinical coordinator trained in EDC operation is authorized to perform data entry.

### **10.2 Data Verification and Review**

The clinical research associate (CRA) should timely check the EDC data against

the original medical documents to ensure the data are accurate, complete, consistent and standardized. Clinical Data Administrator shall review EDC data according to the Data Verification Plan to ensure the data logic, completeness and standardization.

### **10.3 Data Cleaning**

Data cleaning methods include edit check of EDC system, SAS program verification and manual verification. CRA or Clinical Data Administrator raised a query on the trial data found in EDC in a timely manner, and the Investigator or Clinical Coordinator answered the query or corrected the data in a timely manner. If the query was resolved, the query was closed. If the query still existed, it was required to raise a query for further confirmation, until the query was finally resolved.

### **10.4 Electronic Signatures**

After data cleaning, the investigator finally confirmed the authenticity and accuracy of the entered data, and electronically signed the data in EDC. The investigator who performed the electronic signature was required to sign an Electronic Signature Statement prior to implementation stating that the electronic signature had the same legal effect as a written, handwritten signature.

### **10.5 Database Lock**

All the trial data are entered, data verification, data review and query resolution are completed, electronic signature is completed, medical verification is completed, and after the data review report is finalized, a data review meeting is held to jointly confirm the relevant matters before locking. After the Clinical Data Manager confirms the completion of database lock list, perform database lock. In principle, the database will not be unlocked after locking.

### **10.6 Data Transfer**

After the database is locked, the Clinical Data Manager exports the data for submission to the Statistical Analyst and exports the subject eCRFs to each site for archiving.

## **11. Statistical Analysis**

## 11.1 Analysis Populations

Full Analysis Set (FAS): All the subjects who were enrolled and took the study drug at least once were included in the FAS. The following situations may lead to the exclusion of the enrolled subjects from the FAS: they did not meet the main criteria; they did not take the study drug once; they did not have any data after enrollment. Full analysis set is used for analysis of baseline and demographic data;

Safety Analysis Set (SS): all subjects who used the study drug at least once and had safety evaluation data; the safety population will be used for the analysis of safety data.

Effective Analysis Set (EAS): all enrolled subjects who have received at least one dose of the study drug and have at least one efficacy evaluation indicator. The purpose of this data set is to analyze the efficacy indicators of subjects.

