| Data Analysis and Statistical Methods | 
Efficacy Analysis
 
➤ Primary endpoints:
 
Objective response rate (ORR): The percentage of subjects with complete response (CR) and partial response (PR) among evaluable efficacy subjects will be calculated, and the proportion of objective response cases (CR + PR) in the total number of cases will be calculated, with 95% confidence interval (CI). The 95% CI for ORR was calculated based on the exact binomial method using the F-distribution.
 
➤ Secondary endpoints:
 
Disease control rate (DCR): The percentage of subjects with complete response (CR), partial response (PR) and stable disease (SD) among evaluable efficacy subjects will be calculated, and the proportion of the number of cases with disease control (CR + PR + SD) in the total number of cases will be calculated, along with 95% confidence interval (CI). The 95% CI for DCR was calculated based on the exact binomial method using the F-distribution.
 |

|                          |                                                                                                                                                                                                                                                                                                                                                                                                                                                                                                                                                                                                                                                                                                                                                                                                                                                                                                                                                                                                                                    |

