#### **4.5 Exclusion criteria**

Subjects will be excluded if they meet any of the following criteria:

- 1) Patients who do not meet the inclusion and exclusion criteria are included in this study by mistake;
- 2) Wrong dose and method of administration;
- 3) Use of other chemotherapy, surgical treatment or investigational drug other than those specified in this protocol during the trial;
- 4) A serious deviation or violation of the protocol that affects the evaluation of the safety or efficacy of the investigational product.

The final eliminated cases shall be subject to the division decision of statistical analysis data set.

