### **11.3.7 Evaluation of Anti-tumor Clinical Efficacy**

The anti-tumor efficacy of TQB2858 injection will be preliminarily evaluated in this trial. Efficacy analyses were based on the Efficacy Assessment Analysis Set (EAS). Efficacy evaluation indicators mainly include: objective response rate (ORR), disease control rate (DCR), progression-free survival (PFS), overall survival (OS) and duration of response (DOR), 3-month ORR, etc.

Objective response rate (ORR): The proportion of objective response cases (PR + CR) in the total number of cases and its 95% CI will be calculated. The 95% CI for ORR was calculated based on the exact binomial method using the F-distribution.

Disease control rate (DCR): The proportion of disease control cases (PR + CR + SD) in total cases and its 95% CI will be calculated. The 95% CI for DCR was calculated based on the exact binomial method of the F-distribution.

Progression-free survival (PFS): PFS and its 95% CI were estimated using the Kaplan-Meier method, and Kaplan-Meier curves were plotted.

Overall survival (OS): OS and its 95% CI will be estimated using the Kaplan-Meier method and the Kaplan-Meier curve will be plotted.

Duration of response (DOR): Kaplan-Meier method was used to estimate DOR and its 95% CI, and Kaplan-Meier curve was plotted. Only analyzed for responders.

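### Efficacy is analysed only in subjects with an efficacy evaluation, so treated subjects never assessed drop out of the ORR and DCR denominators and both rates can only rise

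*Protocol*

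**What the plan says.** Section 11.1 of the protocol defines three sets. The full analysis set (FAS) is enrolled subjects with at least one dose, and its only stated use is: "Full analysis set is used for analysis of baseline and demographic data". The safety set is for safety. The EAS is "all enrolled subjects who have received at least one dose of the study drug and have at least one efficacy evaluation indicator", and its role is stated: "The purpose of this data set is to analyze the efficacy indicators of subjects".

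Section 11.3.7 confirms the assignment, "Efficacy analyses were based on the Efficacy Assessment Analysis Set (EAS", and lists ORR, DCR, PFS, OS, DOR and 3-month ORR as the efficacy evaluation indicators. No efficacy analysis in all treated subjects is mentioned, even as a sensitivity analysis. No rule says how a treated subject without an assessment is counted.

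The synopsis names two denominators for ORR in one sentence: "among evaluable efficacy subjects will be calculated, and the proportion of objective response cases (CR + PR) in the total number of cases will be calculated". The DCR text has the same structure. Section 11.3.7 mentions only the total number of cases, directly after placing efficacy on the EAS.

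Other relevant text:
- The first scheduled post-baseline scan is at C2D21, about week 6, with a window of ±7 days (Sections 6.2.2 and 8).
- PFS runs from first dose and OS from first treatment. Death is an event for both (Section 8).
- The FAS may lose subjects for three reasons: "they did not meet the main criteria; they did not take the study drug once; they did not have any data after enrollment".
- Section 4.5 lists grounds for excluding subjects, among them "Use of other chemotherapy, surgical treatment or investigational drug other than those specified in this protocol during the trial".

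**The concern.** ORR is the primary endpoint of a single-arm trial with no hypothesis test (Section 11.3.2), so the estimate and its exact interval are the result. There is no control arm to share a bias.

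Entry to the efficacy set depends on something that happens after treatment starts. If an assessment is required, the subjects left out include those who did worst: deaths before week 6, and subjects who withdrew consent or were lost before a scan. Leaving them out removes failures from the denominator and nothing from the numerator. Cohorts may be as small as 10 (Section 11.2), where one subject matters.

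For PFS and OS the clock starts at first dose or first treatment. A set that requires a later scan would condition on surviving to that scan, although OS needs no scan at all.

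**Working it through.** The plan states no target ORR, power or derived sample size, so there is no design figure to reproduce. The check is on the denominator.

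**Inputs.** The cited pembrolizumab sarcoma study in Section 1.1 gives, for soft tissue sarcoma, 7 responders in 40, median PFS 18 weeks and median OS 49 weeks. Cohort sizes are from Section 11.2, and the interval is the exact binomial of Section 11.3.7. The share f of treated subjects with no assessment is not in the protocol and is assumed at 5%, 10% and 20%.

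**ORR and DCR.** With r responders among n treated, the all-treated rate is r/n and the EAS rate is r/(n − fn) = (r/n) × 1/(1−f). The factor is 1/0.95 = 1.05, 1/0.90 = 1.11 and 1/0.80 = 1.25. The same holds for DCR, because an unassessed subject has no recorded disease control.

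| Treated, responders | Left out | All treated (95% CI) | EAS (95% CI) |
|---|---|---|---|
| 40, 7 | 2 | 17.5% (7.3–32.8) | 7/38 = 18.4% (7.7–34.3) |
| 40, 7 | 4 | 17.5% (7.3–32.8) | 7/36 = 19.4% (8.2–36.0) |
| 40, 7 | 8 | 17.5% (7.3–32.8) | 7/32 = 21.9% (9.3–40.0) |
| 10, 2 (illustrative) | 1 | 20.0% (2.5–55.6) | 2/9 = 22.2% (2.8–60.0) |

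**OS, if unscanned early deaths are excluded.** Assume exponential survival with median 49 weeks. Survival to week 6 is 2^(−6/49) = 0.919, so about 8.1% die before the first scheduled scan. If all of them are left out, the curve becomes S(t)/S(6). The median reads 49 + 6 = 55 weeks, and 52-week OS reads 0.479/0.919 = 52.2% instead of 47.9%.

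**PFS, same assumption.** Progression on imaging needs a scan, so those subjects are in the EAS; only unscanned deaths are lost. With an exponential median of 18 weeks and 8.1% removed, the median solves S(t) = 0.5 × 0.919. That gives 18 × (1 + 6/49) = 20.2 weeks. This is a ceiling, because it treats every death before week 6 as unscanned.

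**The case against.** **The entry condition is ambiguous.** Section 11.1 asks for an efficacy evaluation indicator and does not name a scan. Section 11.3.7 lists OS among the indicators. On that usage a subject who dies in week 3 has an OS outcome and belongs in the EAS. This stands: a reader might infer that early deaths are certainly lost from PFS and OS, and the text does not settle that. The synopsis wording about evaluable subjects favours the tumour-assessment reading, and an undefined entry condition for the primary set needs repair in any case.

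**Many early discontinuers will be scanned.** The end-of-treatment visit includes imaging unless progression is already documented (Section 6.2.5). Suspected progression calls for an unscheduled assessment (Section 8). Subjects who stop without progression stay on the imaging schedule (Sections 4.3.3, 6.2.6 and 8). Eligibility requires ECOG 0–1 and life expectancy above 3 months (Section 4.1). So not every early drop-out is excluded. The residue is unscanned deaths, consent withdrawals and losses, and f may sit near the low end of the range.

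**A larger PFS shift is not supported.** Removing the earliest 20% of PFS events would move an 18-week median to 23.8 weeks. Most such events would be progressions seen on a scan, and those subjects stay in the EAS. A living drop-out censored near day 1 hardly changes the Kaplan–Meier estimate.

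**Section 4.5 and the FAS clauses.** A reader might infer that subjects who switch to other anticancer treatment are removed from efficacy. Section 4.5 defers removals to the later division of data sets, and the EAS definition has no such exclusion. The FAS clauses conflict with that set's opening sentence but cannot bias ORR while the FAS serves only baseline data.

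**Preliminary efficacy, and a possible SAP.** No decision threshold is at stake, and detail may be left to an SAP, which was not available here. But the protocol itself fixes the efficacy set, and an SAP that follows it inherits the problem.

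**Conclusion.** The point holds for ORR and DCR, on the reading that EAS entry needs a post-baseline tumour assessment. The direction is then certain whenever at least one treated subject is unassessed and at least one subject responds (for DCR, has disease control). The size depends on f, which the protocol does not give: a factor of 1.05–1.25 for an assumed 5–20%, with the imaging rules pointing to the lower part.

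For PFS and OS the point is conditional. If unscanned early deaths are excluded, the illustration gives a median OS of about 55 instead of 49 weeks and a median PFS of at most about 20 instead of 18. Both assume exponential times and the cited study's medians. DOR is not affected, because it covers responders only.

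The documents do not support saying that early deaths certainly disappear from OS, that all early drop-outs disappear, or that Section 4.5 itself alters the efficacy set.

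**What to change.** Wording changes in Sections 11.1, 11.3.7 and 4.5 and in the synopsis:

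1. Make all subjects with at least one dose the primary set for ORR, DCR, PFS and OS. The FAS can serve if its exclusion clauses, other than never having been dosed, are removed.
2. Count a treated subject without a post-baseline assessment as a non-responder and as not disease-controlled.
3. Keep death without a scan as an event for PFS and OS. Censor a living subject without a scan at day 1 for PFS only; for OS, censor at the date last known alive.
4. Define the EAS explicitly as at least one post-baseline tumour assessment, and keep it as a labelled supportive analysis.
5. State that removals under Section 4.5 do not affect the primary set.
6. In the synopsis, delete the restriction to evaluable subjects and keep the total number of treated subjects as the single denominator for ORR and DCR.

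The cost is a slightly less favourable ORR and one extra supportive table. No additional subjects, visits or data are needed.
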